## Abstract

Simulation-based medical education has been shown to be more effective but also logistically demanding and costly compared to other educational strategies in developing medical skills. Immersive virtual reality is an emerging technology enabling learners to train without a facilitator through computer-generated feedback, offering the potential for increased flexibility in the timing and location of the training and reduced costs. However, little is known about whether immersive virtual reality simulation yields similar results with and without a facilitator. The aim of this study is to compare the effects of self-guided compared to facilitator-guided debriefing for immersive virtual reality simulation-based pediatric emergency team training. We will conduct a randomized, controlled, single-blinded non-inferiority study with a parallel group, pretest-post-test design. 88 medical students (44 teams) will be randomized to undergo immersive virtual reality simulation-based pediatric emergency team training with either self-guided or facilitator-guided debriefing. We will assess the teams before and after the virtual reality intervention in a mannequin-based simulation. The mannequin-based simulation will be videorecorded, and two independent raters, blinded to group allocation, will assess the recordings using validated scales measuring teamwork skills (primary outcome), ABCDE adherence, and time to critical actions. We will further collect data on perceptions of debriefing quality, motivation, workload, usability, and cybersickness. To account for repeated measures and clustering within teams, we will apply a linear mixed model for data analysis. This study aims to provide insight into the effects of self-guided versus facilitator-guided debriefing in immersive virtual reality simulation, with implications for the future development and implementation of immersive virtual reality simulation in medical education.

We have registered the trial on ClinicalTrials.gov (identifier: NCT06956833).

## Introduction

Simulation-based medical education has been shown to significantly enhance the skills of healthcare professionals and students, as well as improve patient outcomes [1–6]. Several systematic reviews and meta-analyses have demonstrated that simulation-based medical education outperforms traditional clinical education and other educational strategies in improving a wide range of medical skills [4,5]. However, simulation-based medical education is also more logistically demanding and costly compared to many other educational strategies [5], prompting calls for research into strategies that maximize its benefits while increasing access and minimizing costs [7].

Immersive virtual reality (VR) is an emerging technology within simulation-based medical education [8–11]. Recent research suggests that VR can provide learning outcomes comparable to other simulation modalities, while potentially offering greater flexibility in training schedules and reducing costs [9,11]. One of its main advantages in enhancing flexible use and reducing costs is the potential reduction in educational professionals needed to facilitate the simulations, as VR scenarios can be programmed to adapt dynamically to learners’ actions, allowing learners to train independently of a facilitator [12]. However, little is known about whether the presence of a facilitator significantly influences the effectiveness of VR simulation.

In simulation-based medical education, the facilitator plays a key role in guiding the debriefing conversation [13]. Debriefing, described as a structured reflection aiming to explore and learn from the simulation-based experience [14,15], has been shown to significantly enhance clinical performance outcomes [16–20]. While facilitator-guided debriefing is widely regarded as the gold standard [13], learners can also lead their own reflection through *self-guided debriefing* [14]. In such cases, the debriefing is typically supported by cognitive aids, such as recordings of the simulation or a debriefing framework, to support self- and peer-assessment [14,21].

The self-guided approaches are grounded in theories of self-regulated learning, such as self-determination theory, which suggest that autonomy may enhance learner engagement and motivation [22]. Research suggests that self-guided approaches may offer additional benefits, including increased ownership and commitment to change [23], flexibility in the duration of the training [24,25], and greater motivation for self-regulated learning [26]. However, learners with lower self-regulation skills may struggle to evaluate their own performance, perceive the process as less effective, be less motivated, and experience increased cognitive load [25,27,28].

While self-guided and facilitator-guided debriefing have been compared in other domains of simulation-based medical education, such as mannequin- and screen-based simulation [18,21,29], little is known about the effectiveness of self-guided debriefing in VR [30]. For VR to fulfil its potential as an independent and scalable simulation-based medical education modality, it is essential to determine whether self-guided debriefing can match the effectiveness facilitator-guided debriefing in a VR context.

### Previous studies on immersive VR in simulation-based emergency training

Little is known about the effect of immersive VR on teamwork skills. This represents a significant gap in the literature, as effective teamwork and communication are critical to preventing patient harm [31–33]. In the field of emergency training, VR has shown promising results for improving the individual skills of healthcare professionals and students, such as clinical reasoning and task prioritization [34–38], triage in mass causality incidents [39], memorization of the ABCDE approach [40], and neonatal resuscitation skills [41]. However, there has been a recent call for research on the effect of VR on *team-based* skill performance and process measures [10]. Further, while one of the proposed key advantages of VR is the possibility of facilitator-independent training, little is known about the role of the facilitator and different debriefing methods in VR for emergency training [10].

### Pilot study

We conducted a randomized, controlled, single-blinded pilot study with parallel group, pretest-posttest design from September to December 2023 [30]. We randomized 24 healthcare professionals (trainee doctors and nurses) from four pediatric units at Copenhagen University Hospital, Rigshospitalet, to participate in VR simulation-based pediatric emergency team training with either self-guided or facilitator-guided debriefing. Teams were assessed at baseline and at one month follow-up in a mannequin-based pediatric emergency simulation. Two independent raters blinded to group allocation assessed team performance based on video-recordings of the mannequin-based simulations. Participants completed questionnaires on their perceptions of debriefing quality, motivation, usability, and workload.

Both interventions were found acceptable and usable. However, nearly half of the participants reported some degree of cybersickness, prompting recommendations to reduce VR exposure, ensure breaks between immersions, and optimize headset alignment. Additionally, coordinating clinically working healthcare professionals across four pediatric units to participate at across three time points proved logistically challenging. To support recruitment feasibility and reduce loss to follow-up in a definitive trial, we decided to limit data collection time points and include participants with more flexible schedules, such as students.

Preliminary results showed significant improvements from baseline to follow-up in both groups for teamwork skills (facilitator-guided mean 1.2, confidence interval (CI) 0.5 to 1.9, p = 0.005; self-guided mean 1.4, CI 0.8 to 2.0, p < 0.001) and ABCDE adherence (facilitator-guided mean 0.5, CI 0.1 to 1.0, p = 0.02; self-guided mean 0.5, CI 0.1 to 0.9, p = 0.01). The facilitator-guided group rated the debriefing quality higher (mean difference 1.4, CI 0.1 to 2.7, p = 0.04), but usability, workload, and motivation were similar across debriefing groups. We concluded that a study designed for testing a non-inferiority hypothesis can be relevant for conclusive evidence.

### Aims and research questions

The aim of this study is to evaluate the effects of immersive VR simulation-based pediatric emergency team training with self-guided versus facilitator-guided debriefing in a randomized, controlled, non-inferiority study with parallel-group, pretest-posttest design.

For the primary outcome, we will investigate the following research question:

**Research question 1 (RQ1 – effect on teamwork skills)**

Does VR-based pediatric emergency team training with self-guided debriefing yield a non-inferior effect on medical students’ non-technical team performance (teamwork skills) compared to VR with facilitator-guided debriefing?

For the secondary outcomes, we will investigate the following research questions:

**Research question 2 (RQ2 – effect on overall team performance)**

Do the two interventions result in a similar effect on medical students’ technical team performance (ABCDE adherence and time to critical actions)? (RQ2a)

Does VR improve overall team performance (teamwork skills, ABCDE adherence, and time to critical actions) in both intervention groups? (RQ2b)

**Research question 3 (RQ3 – perceived effectiveness and engagement)**

Do the two interventions result in a similar engagement in VR simulation and debriefing (intrinsic motivation and perceived debriefing quality)?

**Research question 4 (RQ4 – cognitive load)**

Do the two interventions result in a similar cognitive load?

**Research question 5 (RQ5 – usability and cybersickness)**

What is the incidence of cybersickness and the perceived usability of VR in the two interventions?

## Methods

### Setting and population

The study will be conducted at Copenhagen University Hospital, Rigshospitalet, and Odense University Hospital, Denmark. Eligible participants will be medical students enrolled at Faculty of Health and Medical Sciences, Copenhagen University and University of Southern Denmark, who are within two years of graduation. Exclusion criteria will be lack of informed consent.

Participants will be recruited between May and October 2025 via emails sent to the consultants responsible for medical students’ clinical placements at pediatric departments in the Capital Region of Denmark, Region Zealand, and the Region of Southern Denmark. These consultants will be encouraged to inform medical students, both in person and via email, about the opportunity to participate in the study. Additionally, information and invitations to participate will be shared on social media platforms targeting medical students in the relevant regions. Written informed consent, including permission to record and store all video data for the research project, will be obtained from all participants upon enrolment.

### Study design

We will conduct a single-blinded, randomized controlled non-inferiority study with parallel-group, pretest-posttest design, following the Standard Protocol Items: Recommendations for Interventional Trials (SPIRIT) statement on clinical trial protocols [42].

Teams of medical students will be randomized at a 1:1 allocation ratio to go through immersive VR simulation-based pediatric emergency team training with self-guided or facilitator-guided debriefing. To evaluate the effect of the interventions on team performance, the teams will be assessed managing a mannequin-based pediatric emergency before and after the intervention (Fig 1). The mannequin-based simulation will be video recorded, and two independent observers blinded to group allocation will rate the collective performance of each team based on the videos.

**Fig 1 pone.0332309.g001:**
[figure not shown]
Participant timeline: Schedule of enrolment, interventions, and assessments as recommended by the 2025 SPIRIT statement. * Enrolment and allocation will take place 1–8 weeks prior to t1. t1, t2, and t3 will be conducted in the morning, midday, and afternoon of the same day, respectively. ABCDE: airways, breathing, circulation, disability, and exposure; CTS: clinical teamwork scale; DASH-SV: debriefing assessment for simulation in healthcare student version; IMI: intrinsic motivation inventory; NASA-TLX: national aeronautics and space administration task load index; SUS: system usability scale; VR: virtual reality; VRSQ: virtual reality sickness questionnaire.

### Interventions

Both interventions will last four hours, including one hour of immersive VR simulation and one hour of debriefing (Fig 2). To minimize cybersickness, participants will spend at least 30 minutes outside the VR environment between scenarios. If cybersickness symptoms occur, they will be prompted to exit the simulation and continue by observing on a screen, providing supervision to their teammate.

**Fig 2 pone.0332309.g002:**
[figure not shown]
Illustration of pretest, posttest, and intervention phases. The self-guided group will receive a debriefing script based on the Promoting Excellence And Reflective Learning in Simulation (PEARLS) framework [43] adapted for VR and self-guided use [30,44]. No facilitator will be present, but participants may request technical support. A research assistant will introduce the VR simulation, administer questionnaires, and confirm that all scenarios and debriefings were completed.

In the facilitator-guided group, a medical doctor with formal training and experience in simulation and debriefing will guide the debriefings using the same VR-modified PEARLS framework as the self-guided group. This ensures that the only planned difference between groups is the presence or absence of a facilitator [30,43].

### Development of immersive VR pediatric emergency scenarios and core game mechanics

Three immersive VR scenarios were developed and tested in our pilot study [30]. The scenarios depict three pediatric emergency cases: sepsis, respiratory distress, and anaphylaxis. Interactive elements are embedded in the virtual environment and trigger predefined changes in the patient’s vitals and clinical condition. Dropdown menus are used to simulate palpating of the patient. Participants will navigate the emergency room via teleportation. The cases were developed by [name], [name], [name], and [name]; validated by [name], [name], [name], and [name]; and implemented in UbiSim’s© VR platform by [name] and [name] Scenarios will be delivered using Oculus Quest 2 headsets.

### Development of assessment scenarios

The pretest and posttest assessment scenarios depict an 8-year-old with asthma and a 3-month-old with pneumonia. Participants will perform the scenarios in a mannequin-based simulation to ensure that any improvement in team performance is not due to familiarization with the VR simulation. To reduce potential carryover or learning effects between pre- and post-intervention assessments, distinct but comparable scenarios are used at each time point. Scenarios are matched in complexity and learning objectives but differ in content to minimize practice effects. The two assessment scenarios were tested in our pilot study and found to be similar in difficulty level [30]. [name], [name] and [name] created the cases, with revisions from [name], [name], [name], and [name]

### Outcome measures

Outcome measures and assessment tools are further described in Table 1.

**Table 1 pone.0332309.t001:** Assessment tools, research hypothesis, and outcome measures.

	Assessment tool	Research question	Outcome measure
Team-level outcome (n = 22 teams in each arm)	**Primary outcome**		
	**Clinical Teamwork Scale (CTS®)** [45] − 15 teamwork skills in five main domains: overall teamwork, communication, situational awareness, decision-making − 11-point Likert scale ranging from 1 = unacceptable to 11 = perfect	RQ1: Is the change from pretest to posttest in the self-guided group non-inferior compared to the facilitator-guided group, with a non-inferiority margin of 0.5? RQ3: Is there a significant increase from pretest to posttest in both groups?	Mean CTS score (mean across 15 items and across the two raters.)
	**Secondary outcomes**		
	**ABCDE checklist** [46] − 20 items related to paediatric ABCDE assessment - Checklist ranges from 0 = not initiated to 3 = performed consistently during the whole simulation	RQ2: Is the change from pretest to posttest in the self-guided group comparable to that in the facilitator-guided group? RQ3: Is there a significant increase from pretest to posttest in both groups?	Mean ABCDE checklist score (mean across 20 items and across the two raters.)
	**Time to critical actions** Time (in seconds) to three predefined actions. If the team does not perform the action, they will be assigned a time of 600 seconds (maximum length of scenario).	RQ2: Is the change from pretest to posttest in the self-guided group comparable to that in the facilitator-guided group? RQ3: Is there a significant increase from pretest to posttest in both groups?	Mean time (mean across the three predefined critical actions and across the two raters.)
Individual level outcomes (n = 44 participants in each arm)	**Debriefing Assessment for Simulation in Healthcare Student Version (DASH-SV)** [47] − 6 items related to perceived effectiveness of the debriefing − 7-point Likert scale ranging from 1 = extremely ineffective to 7 = extremely effective	RQ4: Is the mean in the self-guided group comparable to that in the facilitator-guided group?	Mean DASH-SV score (mean across six items and across the three debriefings)
	**Intrinsic Motivation Inventory (IMI)** [48] − 7 items from the interest/enjoyment dimension, related to participants motivation. − 7-point Likert scale ranging from 1 = not at all true to 7 = very true	RQ4: Is the mean in the self-guided group comparable to that in the facilitator-guided group?	Mean IMI interest/enjoyment score (mean across seven items)
	**NASA Task Load Index (NASA-TLX)** [49]. - Six items related to participants perceived workload. - Scale ranging from 0 to 21. Scores are subsequently converted into a single score from 0-100.	RQ5: Is the mean in the self-guided group comparable to that in the facilitator-guided group?	Mean NASA-TLX score (mean across six items)
	**System Usability Scale (SUS)** [50] − 10 items related to perceived usability. - Likert-scale ranging from 1 = strongly disagree, 5 = strongly agree. The scores are subsequently converted into a single SUS score from 0-100 [50].	Exploratory – descriptive statistics	Mean SUS score (mean across ten items)
	**Virtual Reality Sickness Questionnaire (VRSQ)** [51] − 9 symptoms of cybersickness - Likert-type scale ranging from 0 = none to 3 = severe.	Exploratory – descriptive statistics	Mean VRSQ score (mean across 9 items)

ABCDE, airways, breathing, circulation, disability, and exposure; NASA, national aeronautics and space administration task load index; RQ, research questions.

Baseline characteristics will be collected on all participants prior to the intervention, including gender, age, current semester, and prior experience in simulation-based training, computer games, and immersive VR.

#### RQ1- effect on teamwork skills (primary outcome).

Two independent raters blinded to group allocation will rate teamwork skills in the pretest and posttest videos using Clinical Teamwork Scale (CTS) [45]. CTS is designed and validated to rate teamwork skills in simulated pediatric emergencies [45]. CTS has been professionally translated to Danish and demonstrated excellent interrater reliability in our pilot study [30].

#### RQ2 – effect on overall team performance (secondary outcomes).

Two independent raters blinded to group allocation will rate team performance in pretest and posttest videos using the ABCDE checklist, time to critical actions, and CTS.

The ABCDE checklist is modified from the checklist by Hultin et al [46], and measures adherence to the European Pediatric Advanced Life Support guidelines on ABCDE assessment [30,52]. The checklist has demonstrated high interrater reliability in our pilot study [30].

Time to critical actions will be measured as time to each of the following predefined actions: administration of oxygen (pneumonia case) or beta2 agonist (asthma case), administration of fluid bolus 10 mL/kg body weight, and completion of ABCDE assessment.

#### RQ3 – perceived effectiveness and engagement (secondary outcomes).

Participants will complete the Debriefing Assessment for Simulation in Healthcare Student Version (DASH-SV) [47] and Intrinsic Motivation Inventory (IMI) [48].

DASH-SV is a validated questionnaire designed for learners to evaluate the effectiveness of a debriefing. For the self-guided group, ‘The instructor’ was replaced with ‘We’ in consultation with the DASH-SV© developers to reflect the self-guided context, e.g., replacing “The instructor provoked in-depth discussions that led me to reflect on my performance” with “We provoked in-depth discussions that led me to reflect on my performance”.

IMI is a validated measure of intrinsic motivation related to a specific activity [48]. In this study, we will use the 7-item interest/enjoyment subscale, which is considered the direct measure of intrinsic motivation. IMI and DASH-SV have previously been translated professionally to Danish and tested in a Danish context [30,53].

#### RQ4 – cognitive load (secondary outcomes).

Participants will complete the validated NASA Task Load Index (NASA-TLX) [49], a tool designed to assess perceived workload. A professional Danish translation has previously been completed [30].

#### RQ5 – cybersickness and usability (secondary outcomes).

Participants will report symptoms of cybersickness using the validated Virtual Reality Sickness Questionnaire (VRSQ) [51], and perceived usability will be assessed with the validated System Usability Scale (SUS) [50]. SUS has been professionally translated and validated in a Danish context [48]. At the bottom of the VRSQ, we will add a field asking participants to indicate the duration of their symptoms.

### Data collection and management

Participant recruitment will take place from May 6^th^, 2025, to October 31^st^, 2025. Data collection began on May 6^th^, 2025, and is expected to be completed by November 2025. Results are anticipated by June 2026. Schedule of enrolment, interventions, and assessments is presented in Fig 1.

Teams will be assessed before the intervention managing a mannequin-based pediatric emergency (pretest) and again after the intervention (posttest). The mannequin-based simulation will be video recorded and two independent, blinded raters will rate team performance based on the videos. Teams will be randomly assigned one case at pretest and complete the other at posttest. Scenarios will be recorded using a GoPro HERO 4 camera. The raters will be a medical doctor and a medical student, both trained and experienced in assessing team performance using these instruments.

Additionally, after the intervention all participants will complete questionnaires on perceived debriefing quality, motivation, workload, cybersickness, and usability (Table 1 and Fig 1).

Pretest and posttest videos will be stored on a secure hospital drive as logged files, accessible to only to authorized study personnel and are permanently deleted after completion of analyses. All other data will be stored in a secure online database (REDCap) [54] and be pseudonymized before imported into R (version 4.1.2) for statistical analysis [55].

### Sample size calculation

The sample size calculation is based on the assumption that self-guided debriefing is non-inferior to facilitator-guided debriefing for the primary outcome (teamwork skills measured by the CTS© scale.) We set a non-inferiority margin of 0.5 points on the 0–10 CTS© scale, meaning that a difference of less than 0.5 points on the CTS© scale is not expected to constitute a meaningful difference in teamwork skills. The non-inferiority margin was informed by expert consensus, our experience rating teamwork skills in the pilot study, and pilot data [30]. Based on a one-sided two-sample t-test with a non-inferiority margin of 0.5, an alpha of 0.05, a power of 80%, and a standard deviation of 0.63 derived from our pilot data [30], the required sample size is 20 teams (40 participants) in each arm. Assuming a 10% dropout rate, we plan to include approximately 44 participants in each arm, and 88 participants in total. The sample size calculation was performed in R version 4.1.2 [55].

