### Statistical analysis

We will report descriptive statistics on baseline characteristics of each group, reporting continuous variables using median and interquartile range and categorical variables as n/total N (%). Descriptive statistics will be reported for all outcomes at each time point as mean, standard deviations, median, and interquartile range.

We will analyze the team-level data (RQ1 and RQ2) using a constrained linear mixed model with inherent baseline adjustment. Visit (pretest or posttest), assessment scenario (pneumonia or asthma), and the constrained interaction between visit and treatment group (self-guided vs facilitator-guided) will be included as fixed effects. An unstructured covariance pattern will be applied to account for the correlation between repeated measurements and potential changes in variance over time and account for missing data. The mean between the two raters will be calculated prior to statistical analysis.

To analyze individual-level outcomes (RQ3 and RQ4), we will apply a constrained linear mixed model with treatment group as fixed effect and a blocked compound symmetry pattern to account for intra-class correlation between individuals in the same team.

Missing data will be handled within the linear mixed model under the assumption that data are missing at random by including all available data points without requiring imputation. For missing individual-level covariate or questionnaire data, we will first assess the extent and pattern of missingness. If missingness exceeds a minimal threshold of >5%, we will apply multiple imputation using chained equations to account for missing values [57].

For the primary outcome (RQ1), we will report point estimates and two-sided 95% CI. Non-inferiority will be concluded, and the null hypothesis rejected, if the lower bound of the CI exceeds the negative non-inferiority margin [58,59].

For secondary outcomes (RQ2, RQ3, and RQ4), we will report point estimates, two-sided 95% CI, and p-values, and the null hypothesis will be rejected if p < 0.05. RQ5 related outcomes will be reported descriptively using median and interquartile range.

We will adjust for multiple testing using the Holm method to control the family-wise error rate within each family of research questions, except for the primary outcome [58,60].

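### The 80% power is calculated for a one-sided test at 0.05, but non-inferiority is judged on a two-sided 95% CI (one-sided 0.025), where the same t-test gives about 69% to 73%

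*Protocol article*

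**What the plan says.** The Sample size calculation section of the protocol article defines the test used for sizing: "Based on a one-sided two-sample t-test with a non-inferiority margin of 0.5, an alpha of 0.05, a power of 80" per cent. It takes "a standard deviation of 0.63 derived from our pilot data" and concludes that "the required sample size is 20 teams (40 participants) in each arm". A 10% dropout allowance brings this to about 44 participants, or 22 teams, per arm. On the margin it says: "We set a non-inferiority margin of 0.5 points on the 0–10 CTS© scale".

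The Statistical analysis section sets the decision rule: "For the primary outcome (RQ1), we will report point estimates and two-sided 95% CI". The next sentence reads: "Non-inferiority will be concluded, and the null hypothesis rejected, if the lower bound of the CI exceeds the negative non-inferiority margin". No 90% CI and no one-sided 95% bound is mentioned for the primary outcome. The same section plans the team-level analysis as a constrained linear mixed model with baseline adjustment, not as a t-test.

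**The concern.** The lower limit of a two-sided 95% CI leaves 2.5% in the lower tail. Requiring it to lie above -0.5 is therefore a one-sided test at 0.025, twice as strict as the 0.05 used for sizing. The 80% belongs to a test that the trial will not apply.

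At stake is the power statement for the only primary comparison. Readers use that figure to weigh an inconclusive result, and it should describe the rule by which the result is judged. An unreconciled mismatch also leaves room to argue after the fact for a 90% CI, which would double the one-sided error rate of the rule now written.

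**Working it through.** **Inputs.** From the Sample size calculation section: margin Δ = 0.5, SD σ = 0.63, one-sided α = 0.05, power 80%, 20 teams per arm (22 enrolled). From the Statistical analysis section: two-sided 95% CI, hence one-sided α = 0.025. Assumption: true difference 0. The document gives no number for it; 0 is used because it reproduces the stated sample size.

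**Step 1: reproduce the plan's figure.** Normal approximation, teams per arm:

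n = 2σ²(z₁₋α + z₁₋β)² / Δ²

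2 × 0.63² / 0.5² = 0.7938 / 0.25 = 3.1752.

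At α = 0.05: 3.1752 × (1.645 + 0.842)² = 3.1752 × 6.183 = 19.63, which rounds up to the stated 20. The noncentral t gives 79.4% at 20 per arm and reaches 80% at 21, a trivial difference. The plan's figure is reproduced.

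**Step 2: same inputs at the level of the decision rule.** At α = 0.025: 3.1752 × (1.960 + 0.842)² = 3.1752 × 7.849 = 24.92, so 25 per arm. The noncentral t needs 26.

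**Step 3: t-test power.** Noncentrality λ = Δ / (σ√(2/n)), df = 2n − 2. At n = 20, λ = 0.5 / (0.63 × 0.3162) = 2.51; at n = 22, λ = 0.5 / (0.63 × 0.3015) = 2.63. Power is the probability that a noncentral t exceeds the critical value, which at 20 per arm is 1.686 for 0.05 and 2.024 for 0.025.

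| Teams per arm | One-sided 0.05 | One-sided 0.025 |
|---|---|---|
| 20 | 79.4% | 68.6% |
| 22 | 82.8% | 73.0% |
| 25 | 86.9% | 78.5% |
| 26 | 88.1% | 80.1% |

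**Step 4: what baseline adjustment could do.** This step approximates the planned model by a t-test with a reduced SD, assuming equal pretest and posttest variances. If 0.63 is the posttest SD, the adjusted SD is 0.63√(1 − ρ²). If it is the SD of change, the adjusted SD is 0.63√((1 + ρ)/2). Here ρ is the pretest-posttest correlation, which the document does not give, so a range is shown. Power at one-sided 0.025:

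| ρ | Change SD, 20 per arm | Change SD, 22 per arm | Posttest SD, 20 per arm | Posttest SD, 22 per arm |
|---|---|---|---|---|
| 0.3 | 86% | 89% | 73% | 77% |
| 0.5 | 81% | 84% | 81% | 84% |
| 0.7 | 76% | 80% | 93% | 95% |

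The direction in which power moves with ρ depends on which SD 0.63 is, so the two unknowns must be settled together.

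**The case against.** The strongest reply is that the sizing t-test is not the primary analysis. The planned model adjusts for baseline and, by step 4, may well reach 80% at one-sided 0.025 with the teams already planned. This stands as a limit on the conclusion. A reader might infer from the t-test figures that the primary analysis has a 27% to 31% chance of missing true non-inferiority; the document does not support that, because those rates belong to the unadjusted test. The reply does not rescue the stated calculation, though: the article makes no such argument, gives no correlation and does not identify the SD.

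A second reply is that the mismatch is conservative. That is correct: the decision rule is stricter than the sizing alpha, so type I error is not inflated, and the analysis and enrolment are untouched. The error is confined to the power claim.

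A third is that a separate analysis plan may cover the matter. The two conflicting statements both stand in this article, so this is a contradiction and not an omission.

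Some further inferences should not be drawn. The pilot results in the article cannot settle which SD 0.63 is, because it does not report how many teams each pilot arm had. Nor is there a basis for assuming that dropout removes whole teams: testing takes place on a single day, and the model uses all available data. Nothing in the plan says that failing to show non-inferiority would be read as inferiority.

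**Conclusion.** The point holds for the stated calculation. The 20 teams per arm follow from one-sided 0.05; under the stated decision rule the same t-test has about 69% power with 20 teams per arm and 73% with 22. Reaching 80% would take 25 (normal) to 26 (t) evaluable teams per arm, a gap of 5 to 6 teams. These figures rest on the document's margin and SD and on the assumed true difference of 0.

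Whether the trial as it will be analysed falls short of 80% is undetermined. Over correlations of 0.3 to 0.7 and 20 to 22 teams per arm, the adjusted analysis ranges from about 73% to 95%.

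**What to change.** Keep the two-sided 95% CI rule and the 22 teams per arm. In the Sample size calculation section:

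- replace the 80% claim with the t-test power at one-sided 0.025: about 69% with 20 and 73% with 22 analysed teams per arm;
- state the assumed true difference;
- say whether 0.63 is the SD of the posttest score or of the change;
- give the power of the constrained mixed model at one-sided 0.025 over a stated range of pretest-posttest correlations.

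Data collection began in May 2025, so this should be a dated correction made before unblinding. It costs wording and a short calculation, with no additional teams. The downside is that the stated t-test power becomes less favourable.
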